## Abstract

COVID-19 has caused nearly 4.3 million deaths all around the world. People who have experienced loss during this special period may find it difficult to adapt to life after loss, and may even suffer from prolonged grief disorder or other mental health problems. However, there is a huge gap of grief research in China, with almost no comprehensive grief intervention training system or very few professional grief consultants. Considering the large number of bereaved individuals who are suffering from grief and other mental health problems, it is significant to develop a suitable and effective intervention protocol immediately. This article illustrates a study protocol initiated by a Chinese university to investigate the mental health of bereaved individuals during the COVID-19 pandemic and train grief counselors to provide grief counseling to the bereaved, as well as to evaluate the effectiveness of the grief counseling. The method is as follows: (1) 300 psychological counselors will be recruited to attend the grief counseling training. Assessments will be conducted at three time points: baseline (T0), after the basic training (T1), and after the advanced training (T2); (2) 500 bereaved Chinese will be recruit to join the online survey and will be assessed at two time points with a six-month interval; and (3) a two-armed (grief counseling versus wait-list controls) RCT (random control trials) will be conducted with 160 bereaved individuals. Assessments will be conducted at three time points: before randomization (baseline, T0), at the post-counseling (T1), and three months after the post-counseling (T2). Primary outcomes will be assessed by the Prolonged Grief Questionnaire (PG-13), the 20-item PTSD Checklist for DSM-5 (PCL-5), the Depression Anxiety and Stress Scale (DASS-21), and the Posttraumatic Growth Inventory (PTGI). This research will help develop grief research and grief counseling in China, as well as provide professional mental health services for individuals who may suffer from grief-related disorders in the future.

## 1. Introduction

In December 2019, Coronavirus Disease 2019 (COVID-19) was first identified in Wuhan, China. As of 18 August 2021, COVID-19 has caused more than 4.3 million deaths all around the world [1], creating an unprecedented pandemic. A recent study showed that about nine family members would be affected by each death from COVID-19 [2]. Based on this estimate, there will be a huge number of the newly bereaved after COVID-19. In addition, bereaved individuals who have lost their loved ones during the pandemic are also faced with more difficult situations than usual (social isolation, lack of traditional memorial ritual, shortage of medical resources, etc.). Therefore, it is exceptionally urgent to provide appropriate and professional grief counseling or grief therapy for bereaved individuals during this period.

### 1.1. Bereavement and Grief Reactions

Grief is the natural response to losing a loved one. Most individuals adapt to their loss in natural ways. However, there exist substantial variations between individuals in terms of adjustments to loss [3]. In fact, various responses to loss tend to follow several distinct trajectories [4]. After the initial period of losing a loved one, some people could gradually adapt to the new life and move on with their love and memories of the deceased. For others, however, their process of adjusting to the grief is interfered. For a few people, negative mental and physical health consequences are extreme and persistent after bereavement. Individual factors such as maladaptive thoughts, dysfunctional behaviors, or inadequate emotion regulation can largely impede this process [5]. The sudden and unexpected death of a significant individual in one’s life is a highly intense stress event. It can trigger a series of grief reactions, including changes in emotion, cognition, behavior, and physiology [6].

With regard to emotional reactions, the bereaved may have feelings of depression, anxiety, anger, despair, loneliness, longing, and guilt; in terms of cognitive reactions, there may be rumination, self-blame, low self-evaluation, and meaninglessness. At the same time, the bereaved may show behavior reactions such as crying, nervousness, social withdrawal, and repeated search for the deceased. In addition, there may also arise some physiological problems, such as loss of appetite, insomnia, and fatigue [4,6,7,8,9,10]

For most of the bereaved, they can gradually accept the reality of loss and adapt to new life without the deceased under the influence of some factors, such as adequate social support, traditional funeral rituals, and meaning reconstruction [11]. However, studies have suggested that some bereaved people may develop intense and continuous symptoms in emotional, cognitive, behavioral, and physiological aspects, which may lead to the impairment of their mental or physical health and social functions [6,7,10,12].

The topic of grief and loss is a common issue for people all around the world [13]. The establishment of diagnostic criteria will facilitate the development of research and practice in grief field, and the diagnostic criteria applicable to clinical and practical applications will be beneficial to improve clinical utility [14].

In 2018, the 11th edition of the World Health Organization’s new International Classification of Diseases (ICD-11) established prolonged grief disorder (PGD) as one of the stress-related diseases [15]. According to the ICD-11, the diagnosis of prolonged grief disorder should conform to the following criteria: six months after the bereavement, longing for the deceased and/or persistent preoccupation with the deceased, accompanied by strong emotional pain, such as grief, guilt, anger, denying, blaming oneself or others, having difficulty accepting that relatives and friends have passed away, feeling that part of one’s self has passed away with the departure of relatives and friends, unable to experience positive emotions, and emotional numbness [15]. And the symptoms should reach a level where the grief seriously affects one’s own life, work, and social interactions. An important goal of diagnostic evaluation is to identify patients who need support and to provide recommendations on the available treatment [14]. The new diagnosis of PGD in ICD-11 shows a flexible guideline to allow space for more clinical judgement and a classification system with fewer categories [14,16]. It has played a key role in promoting attention to the mental health of bereaved individuals and the development of targeted treatment programs for patients with prolonged grief disorder after bereavement. [16,17].

In addition to prolonged grief disorder, which is a bereavement-specific psychological risk, previous studies have also found that bereaved individuals show increased risk of suffering other mental disturbances and health problems [18], such as depressive disorder [19,20], anxiety disorder [21], post-traumatic stress disorder [22,23], self-harm problems [24], suicidal behavior [25], sleep disorders, substance abuse, immune dysfunction [5], cardiovascular disease and cancer risk. Among bereaved individuals, the prevalence of post-traumatic stress disorder is as high as 10–30%, and there exists a complicated comorbidity with prolonged grief disorder [26,27].

### 1.2. Bereavement and Grief under COVID-19 Outbreak

According to previous studies, the prevalence of prolonged grief disorder in the general bereaved population is approximately 9.8% [28]. Sudden and violent deaths have the potential to lead to a higher prevalence of PGD among the bereaved, from anywhere between 14% and 76% [29].

In this pandemic, bereaved individuals are faced with countless difficulties and challenges. Due to the contagious nature of the virus, relatives are often unable to visit, take care of, or even check in on the patients. Many people experience this loss without preparation. In addition, due to the quarantine policy, it is impossible to hold the traditional Chinese family-gathering memorial ritual after the death. The life of the majority of bereaved individuals have been greatly affected by the virus, and some bereaved individuals have even experienced the loss of multiple relatives at the same time. The aforementioned difficulties, such as unexpectedness, no farewell rituals, multiple losses, and lack of self-security and so on, may lead to a higher risk of mental disturbances (such as prolonged grief disorder) than usual. A recent study indicated that during COVID-19, the prevalence of anxiety or depression was 20.4% [30]. The high levels of mental health problems may hinder the process of grief adaptation. According to a recent study, researchers found that over one-third of COVID-19 related bereaved Chinese individuals suffered from PGD [31]. The high prevalence demonstrated in the study above validates the importance and urgency of the concerns and early interventions for bereaved individuals due to COVID-19.

### 1.3. Grief Counseling and Grief Therapy

We often say “time will cure everything”. However, for individuals with prolonged grief disorder, they may experience a stronger grief response over time, without the help of professional grief counselors [32]. Moreover, the prolonged grief disorder does not only lead to emotional pain and impaired social function for the patients themselves, but also brings heavy stress and pain to other relatives.

Grief is a natural experience after loss, but for those bereaved who have difficulty adapting to grief, seeking help from psychotherapy is important [33]. Consequently, more research is needed to explore short-term, evidence-based, grief-focused, and effective psychological treatments.

The present grief treatments include: (a) meaning reconstruction [34], emphasizing that reconstruction of lost meaning is an important process of grief adapting; (b) complicated grief treatment (CGT) [5], focusing on the two directions of coping with loss and rebuilding a new life; (c) cognitive-behavioral therapy for complicated grief (CBT-CG) [35], helping individuals to integrate loss experiences into their autobiography through imaginal exposure, cognitive restructuring, and behavioral activation, while reducing negative self-evaluation, dysfunctional beliefs, and their avoidance behavior, and finally achieving the purpose of helping them better adapt to their life after loss.

### 1.4. Grief Research and Grief Counseling in China

There is hardly any systematic grief intervention training system and professional grief consultants in China. In emergencies of major public health crises, the Chinese government often ignores the psychological aspect of the rescue of the people, especially the psychology support for the bereaved. Faced with characteristics of the grief among the bereaved from this pandemic, the gap in grief intervention is particularly prominent. During COVID-19, there may be a great many bereaved individuals who have difficulty adapting to their loss. However, due to the insufficient number of professional psychological counselors, social isolation, and other reasons, the majority of bereaved Chinese can’t gain access to reliable psychology resources. Although western countries have a relatively complete bereavement support and grief counseling system, as well as a professional training system for grief counselors, it remains to be established through empirical studies if it is the case that western protocols are feasible to apply to the situation in China.

### 1.5. Rationale for the Research

In view of the urgency of mental health assistance for the bereaved during COVID-19, we set up a team and designed this present research. Notably, this research is not only a scientific research project, but also a social welfare project. Whether or not the bereaved research participants are willing to have their data collected for this research, we will provide free grief consulting services for more than 160 bereaved individuals during the research period.

The first aim of this project is to train and evaluate Chinese grief consultants with reference to the more developed western grief consultant training system, and to fill the huge gap of grief consulting in China. Secondly, previous studies suggest that related factors (such as unexpected death, social isolation, and multiple losses) may hinder the process of adaptation and recovery of bereaved individuals, but the mechanism remains to be elucidated, so it is necessary to design a longitudinal study to investigate the mental health and associated factors of the bereaved in China [31]. Finally, we set out to develop a grief counseling program suitable for Chinese culture to provide support for bereaved people during COVID-19, while verifying the effectiveness of the design, and supplementing grief research.

The principal research objectives are to:

Investigate demographic and related factors associated with prolonged grief symptoms among Chinese individuals bereaved due to COVID-19 (including grief reaction, trauma response, depression, anxiety, and suicide risk).Develop training and evaluation programs for Chinese professional grief counselors to develop and examine their competence.Provide grief counseling for the bereaved during the pandemic and assess the effect of the intervention.

## 2. Research Design

This research includes three studies, and the overall research framework is shown in Figure 1.

### 2.1. Study 1: Grief Counselor Training and Evaluation

Study one aims to professionally train psychological counselors to be competent to carry out grief counseling. 300 candidates for the program will be recruited. Certain information will be gathered from the candidates, who will be screened for suitability for the program. Training program targeting grief counseling will be designed and implemented to coach these counselors. The training program consists of a basic phase and an advanced phase. A certain competency test will be carried out before the training, and after the two phases of the training to evaluate the effectiveness of the training program.

#### 2.1.1. Sample

Participants can be included in this study if they meet the following criteria:

Educational background: Master’s degree in psychology (consulting and clinical psychology), psychiatry, nursing, or social work.

•Qualifications: (a) Qualified as a registered psychologist, registered social worker, or occupational psychological counselor (national second level); (b) provided more than 500 h of psychological consultation for clients and received at least 50 h of individual supervision or 100 h of group supervision; and (c) received psychological counseling ethics training in the past three years.•Voluntary participation in the whole process of research.•In addition, the consultants who sign up are required to provide the following information for screening: (a) experiential description of grief counseling services; (b) certificate of participating in systematic psychological counseling or treatment training; (c) experience in grief counselling training, crisis intervention training, trauma-related training; (d) personal grief experience; (e) willingness and motivation to participate in grief counseling.

#### 2.1.2. Procedure

A competency test will be given to all counselors who have passed the screening before the training (T0). The competency test will consider three dimensions of competency (knowledge, attitude, and practice) and draw on the competency instrument of the training program of the Complicated Grief Research Center of Columbia University, and it will be adjusted to the context of Chinese psychotherapy. A training program will be designed with the experience from domestic and foreign experts in the field of grief, then a six to eight sessions training will be given to all counselors in basic phase, and advanced phase respectively. After the basic (T1) and advanced (T2) training, the counselors will be assessed again with the same competency test.

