## 3. Statistics Analyses

IBM SPSS Version 25 (Armonk, New York, USA) will be used to analyze the data. Both completer analyses and intention-to-treat analyses (using the method of last observation carried forward) will be carried out. Descriptive characteristics of the sample will be calculated as obtained counts (*n*) and simple proportions (%), with missing items reported as missing.

For study one, the measurements at three different time points will be compared using the analyses of variance (ANOVA) for continuous variables and the chi-square test for categorical variables.

In addition, in study two, the researchers will employ linear regression analyses to examine the predictors of PG-13, DASS-21, PCL-5 and PTGI at each time point, while controlling for gender, age, education level, marital status, and religious beliefs. The cross-lagged model will be used to further clarify the direction of the relationship between the predictors and outcome variables. A *p*-value < 0.05 (2-tailed) will be taken to indicate statistical significance.

For study three, Chi-square tests and ANOVAs will be conducted on baseline scores to rule out significant differences between groups on demographic or loss-related or outcome variables before treatment. The treatment effects on the primary outcome variables will be examined with a 2 (groups) × 3 (time points) multivariate analysis of variance (MANOVA), with three time points (baseline, post-counseling, and three months follow-up) as the repeated measures. The outcomes of treatments will be further investigated separately with the analyses of covariance (ANCOVA), using baseline scores of the outcome variables as covariates.

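### Study 1 has one group, all trained and retested on the same competency test, so a rise in score describes change and cannot show that the training works

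*Protocol article*

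**What the plan says.** Section 2.1 states that "300 candidates for the program will be recruited" and that candidates are then screened. A competency test is given before training and "after the two phases of the training to evaluate the effectiveness of the training program".

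Section 2.1.2 fixes the rest of the design. All counselors who pass screening sit the test at T0. Then "a six to eight sessions training will be given to all counselors in basic phase, and advanced phase respectively". After the basic phase (T1) and the advanced phase (T2), "the counselors will be assessed again with the same competency test". The test covers knowledge, attitude and practice, and is still to be adapted for use in China.

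For the analysis, Section 3 says that "the measurements at three different time points will be compared using the analyses of variance (ANOVA) for continuous variables", with chi-square tests for categorical variables. Nothing else is planned for Study 1.

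The only comparison arm in the article is in Study 3, where the Abstract says "a two-armed (grief counseling versus wait-list controls) RCT (random control trials) will be conducted with 160 bereaved individuals". The Discussion (Section 4) presents the project as the first in mainland China to study the effect of training grief counselors, and says that it evaluates the programme.

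**The concern.** Effectiveness is a causal conclusion: scores are higher than they would have been without the training. Study 1 collects nothing that shows what scores would have been without it. Each counselor sits the same test up to three times, and the T2 result follows two earlier sittings. Any change over that period, from whatever source, enters the same time-point comparison.

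At stake is what the Study 1 result may be used to say. With a sample of this size, a modest gain that owes nothing to the training has a good chance of reaching significance and being reported as evidence that a new national training programme works. A later statistical analysis plan cannot repair this, because the design produces no data that separate the explanations.

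**Working it through.** **1. What the design can identify.** Write the expected change from T0 to T1 as

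change = training + practice on the test + outside experience and time + effect of selective drop-out.

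The change from T1 to T2 has the same four parts. Study 1 observes two changes, and each is a sum of four unknowns. Training cannot be isolated from either. In a randomised untrained group tested on the same dates, practice, outside experience and time would be common to both groups and would cancel in the difference. No such group is planned.

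**2. Is there a figure to reproduce?** No. The article gives no effect size, power or sample-size calculation for Study 1. What follows is an illustration, not a check of a stated number.

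**3. Inputs.**
- n = 300, from Section 2.1. The number tested may be lower, because these are candidates before screening. The Abstract can be read as 300 attending the training.
- Two-sided alpha 0.05. Section 3 says that a p-"value < 0.05 (2-tailed) will be taken to indicate statistical significance". The sentence stands in the Study 2 paragraph and is assumed to apply to Study 1.
- True training effect: zero (assumed, to isolate the problem).
- Non-training gain d, in SD of the change score: assumed 0.10, 0.15 or 0.20.

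**4. Chance of p<0.05 for one paired contrast.** The formula is P = Φ(d√n − 1.96) + Φ(−d√n − 1.96). The second term is negligible here.

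| d | d√300 | minus 1.96 | P |
|---|---|---|---|
| 0.10 | 1.732 | −0.228 | 41% |
| 0.15 | 2.598 | 0.638 | 74% |
| 0.20 | 3.464 | 1.504 | 93% |

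The nominal rate is 5%.

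**5. Sensitivity.**
- *Raw-score units.* The SD of the change is √(2(1−r)) times the raw SD, where r is the correlation between sittings (not given, assumed 0.5 to 0.8). A raw gain of 0.05 SD gives 14% to 28%, 0.10 SD gives 41% to 78%, and 0.20 SD gives 93% to more than 99.9%.
- *Fewer counselors.* With an assumed 20% loss, n = 0.8 × 300 = 240. At r = 0.5 the chance is 34% for 0.10 SD and 87% for 0.20 SD.
- *All three time points.* This uses a repeated-measures F test with 2 and 598 degrees of freedom, means 0, d, d and equal correlations. The noncentrality is n·Σ(μ − mean μ)²/(1 − r). For d = 0.10 raw SD and r = 0.5 it is 300 × 0.00667/0.5 = 4.0, which gives 41%; r = 0.7 gives 63%. For d = 0.20 the results are 96% and 99.8%.

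The planned ANOVA is therefore about as exposed as the single contrast.

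**The case against.** The strongest reply is that every gain in the illustration is assumed. The article gives no retest gain, retest correlation or interval between sittings. At 0.10 SD of the change score a non-significant result is the likelier outcome (41% against 59%), and at 0.05 raw SD the chance is only 14% to 28%. This stands. A reader might infer that the test would come out significant whether or not the training works, but the figures do not support that.

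Three other strong readings also go too far:
- *That the bias always favours the training.* Recall of items plausibly raises knowledge scores. The article gives no basis for saying the same of attitude scores.
- *That practice is the whole problem.* It is one of several uncontrolled explanations.
- *That Study 3 is compromised.* Section 2.3 does not make a Study 1 score a condition for delivering counseling, and the randomised comparison there does not rest on Study 1.

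It can also be said that one instrument keeps scores comparable over time, that the same test need not mean identical items, and that training everyone serves the urgency and social-welfare purpose in Section 1.5. These are fair reasons for the design. They do not make it able to support a causal conclusion, since even with different items there is still no comparison group.

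**Conclusion.** The point holds as a mismatch between the Study 1 design and the conclusion drawn from it. The article itself fixes one group, training for all, the same test three times and a comparison of time points only. That supports a statement about how scores changed, not one about whether training caused the change.

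The size of the distortion is unknown. If training had no effect and about 300 counselors were tested, an assumed gain of 0.10 to 0.20 SD of the change score would be declared significant in about 41% to 93% of cases for one contrast. The conclusion that training cannot be isolated does not depend on those assumptions. The figures only show that a modest non-training gain could well be read as success. The finding is confined to Study 1, a non-randomised part of the project.

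**What to change.** **Main change.** In Section 2.1, state that the competency test is given before training and after each phase in order to describe change in competency score over the training. Add that, without an untrained comparison, the change is not attributed to the training. Make the same change to the claim of a training effect in the Discussion. This needs no new data; its cost is a less favourable claim.

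**Optional, where the sponsor finds it feasible.** The test is still being adapted, so equivalent item sets could be written for the knowledge and practice dimensions and given in counterbalanced order over T0, T1 and T2. This costs item writing and a check that the sets are equivalent. It reduces item-specific practice only and does not restore the effectiveness claim.

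**If the effectiveness claim is to be kept.** It would need counselors randomised to immediate or delayed training, with the delayed group retested before it starts. With 150 per group and baseline-adjusted ANCOVA, the difference detectable at 80% power is (1.96 + 0.84) × √((1 − r²) × 2/150). That is about 0.28 SD at r = 0.5 and 0.23 SD at r = 0.7, both values of r being assumed. No extra counselors are needed, but half would be trained later, which has to be weighed against the urgency stated in Section 1.5.
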